### Setting

The study will be conducted in Santander, Colombia, in four cities: Bucaramanga, Floridablanca, Girón, and Piedecuesta (metropolitan area). The participants will be recruited through three main sources: (1) healthcare providing institutions (IPSs) that collaborate with the study, including hospitals and health centers; (2) private neurology clinics; and (3) the general community through dissemination strategies such as press, radio, television, and personal contact. The Biomedical and Biotechnological Research Laboratory (LIBB) of the Bacteriology and Clinical Laboratory program at Universidad de Santander (UDES) will be used for sample collection for microbiota evaluation and APOE genotype analysis. These samples will be analyzed at the Universidad de Málaga. The design and implementation of the intervention will be carried out through a strategic alliance between the Universidad de Santander (UDES), Universidad Manuela Beltrán (UMB), Universidad Autónoma de Bucaramanga (UNAB), La Universidad Santo Tomás (USTA), Universidad de Málaga, and Fundación Oftalmológica de Santander (FOSCAL). The intervention will be carried out in the patients’ homes, and the family component will be provided through training at the UMB.

### Dyad involvement

The call for participation in the study and the dissemination of inclusion criteria will be carried out in the three recruitment sources through informational posters, flyers, and announcements in radio and television media. Individuals who report amnestic cognitive complaints or have a diagnosis of MCI will be invited to participate, accompanied by a family study partner, and their interest will be expressed via WhatsApp messages or emails. A telephone interview will be conducted for the preselection of candidates, inquiring about their cognitive manifestations and the fulfillment of preliminary inclusion criteria, such as the ability to perform physical activities, the level of independence, cognitive complaints, and the presence of anxious or depressive symptoms. Following this, participants will be formally invited to participate in the study through an informed consent process for both the patient and their family member. Then, comprehensive baseline evaluations for the patient will be carried out by professionals in neuropsychology, nursing, physiotherapy, neurology, and psychiatry in appropriately equipped offices to ensure privacy, the absence of sound interference, and the availability of necessary resources. Similarly, family members will be asked to complete questionnaires regarding social support, quality of life, and caregiver burden. Finally, an adjudication committee composed of a neurologist, a psychiatrist, a neuropsychologist, and an epidemiological nurse will analyze the collected information to confirm the diagnosis of MCI according to the DSM-5 criteria and verify compliance with the established inclusion criteria (see Fig. 1).

**Fig. 1 Fig1:**
[figure not shown]
Flowchart of participant allocation

### Intervention

INTERCOG is a nonpharmacological, multicomponent, and transdisciplinary intervention with a focus on the patient-family dyad. Its components include cognitive training and stimulation, physical training, nutritional counseling, and support for the family study partner. Patients assigned to the intervention group will receive the NPMI INTERCOG for 12 weeks, twice weekly home-based sessions and once weekly independent work session consisting of 10–30 min of daily walking and complete homework.

The home-based sessions will include cognitive training/stimulation, physical training, and nutritional counseling. For their part, family study partners will receive weekly training at a university institution for 12 weeks. The intervention structure for the dyad is described in Table 1. To facilitate the intervention process, two workbooks were developed (one for patient and another for family member) [23, 24], as were video recordings to guide physical activity and nutritional recommendations [25]; detailed 12-week schedule of the intervention is provided in Supplementary Table S1. A distinctive feature of the INTERCOG program is its home-based delivery model. By conducting the intervention within the participants’ domestic environment, we aim to reduce geographical and economic barriers to care—such as travel time and transportation costs—which are often deterrents for older adults and their family study partners in regions like Santander.

**Table 1 Tab1:** The nonpharmacological, multicomponent intervention INTERCOG for MCI focuses on the patient–family dyad, Bucaramanga, and the metropolitan area, Santander, Colombia, 2025

Component	Target domains/clinical goals	Enhanced specific activity examples	Tailoring and progression
Cognitive	Executive function, memory (episodic/working/sensory), attention, calculation, and orientation	Ecological task planning: organizing medication schedules and grocery lists. Neurocognitive training: life-history reconstruction (autopsychic orientation), trail making (visual attention), and arithmetic logic puzzles for mental calculation	3 levels of difficulty per activity (scaffolded progression). Tasks advance from simple stimulus identification to complex multi-step problem solving
Physical	Aerobic capacity, muscular strength, static/dynamic balance, and joint mobility and simultaneous dual task	Dual-task integration: performing verbal fluency tasks while walking. Proprioceptive challenge: lower-limb strength exercises (e.g., squats) performed with eyes open/closed to increase neuro-vestibular demand. Standardized 21-video series for strength, gait, and balance	Progression by intensity: workload is monitored via the Modified Borg Scale, increasing from a baseline of intensity 4 (month 1) up to intensity 8 (month 3)
Nutritional	Glycemic control, brain-health nutrients (omega-3/antioxidants), and dietary habit modification	Interactive nutritional workshops: “cooking laboratories” for preparing functional foods (e.g., quinoa, flaxseed). Behavioral coaching: strategies for sugar reduction and identifying ultra-processed vs. whole-grain carbohydrates	Shift from theory to practice: transitions from basic macronutrient education to the implementation of Mediterranean-style neuroprotective diets in daily life
Familiar	Psychoeducation, communication skills, and prevention of caregiver burden	Empowerment sessions: family reorganization workshops, conflict resolution training, and relaxation therapies. Technological literacy: training on the use of health-monitoring apps and virtual support networks	Focus on resilience: moves from initial program induction and emotional support to the establishment of long-term sustainable caregiving routines

The control group, in addition to usual care, will receive weekly information on the prevention of infectious diseases on their mobile devices. This material, similar to that available online, will be provided as an Enhanced Standard of Care (ESOC) (Supplementary Table S2). Once the study is completed, participants in the control group will receive an intensive 1-week version of the NPMI INTERCOG, as well as the workbooks for the patient and the family member.

### Intervention fidelity and standardization

The INTERCOG intervention will be delivered by a trained multidisciplinary team (nurses, psychologists, physiotherapists, and speech-language pathologists). To minimize inter-interventionist variability, the program utilizes two registered workbooks [23, 24], which contain all standardized cognitive, nutritional counseling, physical, and familiar activities. Prior to the trial, all interventionists will undergo a standardized training program focused on the theoretical foundations of the INTERCOG model and the practical application of the protocols. This training is supported by an instructional video series consisting of 21 standardized physical training sessions (one per session) and 9 videos about nutritional advice. To facilitate real-time access during home visits, the workbooks include integrated QR codes that link directly to the corresponding video demonstrations, ensuring uniform delivery of the exercise components [25].

Fidelity is maintained through a multi-layered strategy: (1) digital process logs: interventionists will use REDCap to record session attendance and qualitative execution reports in real-time; (2) clinical supervision: weekly team meetings to discuss implementation challenges; and (3) direct oversight: co-investigators will perform unannounced home visits and follow-up calls to ensure protocol adherence.

### Outcomes

To evaluate the feasibility, acceptability, and adherence of the intervention as a primary outcome, several dimensions proposed by Gadke et al. [26] will be assessed. Table 2 presents the dimensions, questions, measurements, and possible actions to be taken in the progress of the trial.

**Table 2 Tab2:** Evaluation of feasibility, acceptability, and adherence of NPMI INTERCOG

Dimension	Questions	Measurements	Possible actions
Recruitment and retention capability	What are the difficulties or ease in recruiting dyads? Is it possible to recruit 102 dyads that meet the inclusion criteria?	Number of collaborating institutions contacted, the number of interested individuals, the number of individuals preselected and evaluated, the participant rejection criteria, the number of people who decided not to continue in the trial, and the recruitment rate	Expanding the number of collaborating institutions and ways to disseminate the call for participation or extend it overtime, increasing recruitment staff, and strategies to prevent participants dropouts
Data collection procedures	Are the measurements sensitive enough to determine change? Are the measurement procedures useful? Were any outcomes missing? What are the difficulties or ease in data collection?	Difficulties in data collection, changes in questionnaire cutoff points, completeness of data collection, data collected unnecessarily	Supervision of instrument completion and data quality control Alternative analysis of the variable without cutoff points, or as a continuous variable, or establishment of tertiles or quartiles
Social validity	Do participants perceive the intervention as appropriate, safe, and potentially effective? Are the frequency, intensity, and methods used in the interventions perceived as appropriate? What are the reasons for not participating in an intervention?	Participant surveys and interviews to obtain postintervention feedback data in person and by telephone	Implement strategies to improve understanding of interventions Evaluate the possibility of making any adjustments to the intervention methodology
Practicality	Can interventions be implemented with time, training, available resources/materials?	Interview participants and healthcare professionals to identify implementation challenges related to practicality Availability to acquire materials and supplies for the intervention	Evaluate alternative materials or resources that are easier to acquire, reduce or recalculate intervention times, and retrain staff
Adherence	Do participants comply with the proposed activities?	Completion rate Activity completeness	In the event of difficulties, interview the possible reasons to evaluate alternatives for compliance

Also, the potential efficacy of the NPMI INTERCOG will be evaluated as an exploratory outcome by measuring the change in global and cognitive domains: (1) global cognition: change in the scores of the Montreal Cognitive Assessment (MoCA) as a primary cognitive endpoint [27, 28] and the Mini-Mental State Examination (MMSE) [29, 30]; (2) verbal learning and memory: change in the scores of the Hopkins Verbal Learning Test (HVLT) [31, 32]; (3) processing speed and visual attention: change in scores on the Symbol Digit Modalities Test (SDMT) [32, 33]; (4) visual attention, processing speed, and visuospatial ability: change in the scores of the Trail Making Test (TMT-Forms A and B) [32, 34]; (5) executive function and selective attention: change in the scores of the Stroop Color and Word Test [35, 36]; (6) perceptual organization and visual memory: change in the scores of the Rey–Osterrieth Complex Figure Test [32, 37]; (7) verbal fluency and executive functions: change in the scores of the Semantic and Phonemic Verbal Fluency Test [32]; (8) comprehension and expression levels: change in the scores of the Boston Naming Test [32, 38]; (9) verbal comprehension: change in the scores of the Token Test [39, 40]; (10) digit span: change in the scores of the digit span subtest of the WAIS-III (Wechsler Adult Intelligence Scale-Third Edition) [41]. Descriptions of the measures, scores, cutoff points, and interpretations are described in the trial registry [42].

Among the secondary outcomes, the variation in health-related quality of life will be estimated through the application of the 36-Item Short Form Health Survey (SF-36) to both the patient and the family member [43, 44]. As a primary functional endpoint, we stablished the change in instrumental activities of daily living (IADL) measured through the Lawton and Brody scale [45, 46]; also, the change in the Fried’s criteria of frailty, which includes the assessment of weight loss (weight, body mass index, and waist-to-hip ratio), physical activity, exhaustion, and grip strength, will be evaluated [47, 48]. Nutritional status with the Mini Nutritional Assessment (Long-MNA) [51], and the change in the risk of falls will be evaluated with the Tinetti balance scale [52].

### Data collection procedures

Data collection will be conducted at three time points: (1) during the preselection process, (2) at baseline, and (3) during follow-up (at 3, 6, and 9 months of the study). At each point, a team of professionals from various previously trained disciplines will administer multiple questionnaires and perform measurements. The detailed schedules of the instruments, measurement time points, and evaluators are presented in Table 1.

### Preselection

To identify compliance with the inclusion criteria, the following instruments will be used in the preselection stage: Geriatric Depression Scale (GDS): patients with a score below 10 points will be invited to participate [53]. Barthel Index of Activities of Daily Living (BI-ADL): independence in performing activities of daily living will be evaluated, establishing a cutoff point of 80 or more points to confirm functional independence compatible with the diagnosis of MCI [54]. Physical Activity Readiness Questionnaire for Everyone (PAR-Q & YOU): this will be used to identify the absence of restrictions for physical activity, considering negative responses to 6 of the 7 questions as a participation criterion (the question about medication use will be excluded, considering it a precaution and not a restriction) [55].

### Baseline and postintervention follow-up (0, 3, 6, and 9 months)

Neuropsychological assessment: a neuropsychologist will administer tests to evaluate global cognition, and the cognitive domains will be defined as the primary outcome. Together, these tests provide a detailed profile of the key cognitive areas affected by MCI.

Nursing assessment: measurements of blood pressure and pulse will be taken with an OMROM model HEM-7130 automated monitor. In addition, the following instruments will be administered: the SF-36 Health Survey [49], Patient Characterization Form (basic information, family, pathological, pharmacological, and surgical history), Family APGAR [50], Mini Nutritional Assessment (Long-MNA®) [51], Pittsburgh Sleep Quality Index (PSQI) [52], and Bristol Stool Form Scale (BSFS) [53].

Physiotherapy assessment: dominant handgrip strength will be measured with a JAMAR 6386 hydraulic analog hand dynamometer. Weight and body composition will be assessed by bioimpedance with a Body Composition Monitor and Scale OMRON HBF 514C. Height and waist and hip circumferences will be recorded via a standardized method. Additionally, Tinetti gait and balance assessment tool [54], Senior Fitness Test [55], Linda Fried Frailty Phenotype [47], and Lawton-Brody Instrumental Activities of Daily Living Scale [46] will be administered.

Family member assessment: nursing staff will apply the GCPC-UN-D© sociodemographic form for the characterization of study partner [56]. Social support will also be assessed via the Medical Outcomes Study Social Support Survey (MOS) [57], quality of life with the SF-36 [49], and caregiver burden with the Zarit Caregiver Burden Interview [58, 59] (see Supplementary Table S3 for more details).

### Data management and monitoring

Study data will initially be collected via paper forms and subsequently double-entered into REDCap electronic data capture tools, hosted at the Universidad de Santander [60]. To ensure data integrity, a researcher will audit the database for completeness and resolve discrepancies identified during the double-entry process.

Healthcare professionals delivering the intervention will be trained to recognize and report any potential adverse events (AEs), particularly those related to the physical activity component. All AEs will be immediately reported to the principal investigator and the study’s insurance provider, as detailed in the protection policy.

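### The only adverse-event route described runs through INTERCOG delivery staff, so event counts would not be comparable between arms; one identical question at the existing visits would repair this.

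*Protocol article*

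**What the plan says.** The protocol article's adverse-event text is in Data management and monitoring. It assigns recognition and reporting to one group: "Healthcare professionals delivering the intervention will be trained to recognize and report any potential adverse events (AEs", with emphasis on events from the exercise component. The reporting line follows: "All AEs will be immediately reported to the principal investigator and the study’s insurance provider, as detailed in the protection policy".

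The two arms meet those staff very differently. Under Intervention, "Patients assigned to the intervention group will receive the NPMI INTERCOG for 12 weeks, twice weekly home-based sessions". The control group, "in addition to usual care, will receive weekly information on the prevention of infectious diseases on their mobile devices".

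Both arms are assessed "during follow-up (at 3, 6, and 9 months of the study" (Data collection procedures). Baseline and postintervention follow-up lists the instruments for those visits by discipline. Blinding keeps the assessors separate from the intervention staff.

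Safety enters the feasibility questions once, under Social validity in Table 2: "Do participants perceive the intervention as appropriate, safe, and potentially effective". It is measured there by surveys and interviews. The three benchmarks in Feasibility analysis and success thresholds are recruitment, retention and adherence.

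**The concern.** The people trained to notice and report events are the people who visit one arm. If the text is followed as written, the chance that an event is recorded depends on allocation. That is more than an omitted detail, because the article does state a capture mechanism and the mechanism belongs to one arm.

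This matters because the physical component is progressive. Table 1 raises effort from 4 to 8 on the Modified Borg Scale over three months and includes dual-task walking and strength work with eyes closed. Some falls, injuries and admissions will occur in older adults whatever their allocation. A pilot meant to inform a larger trial needs that background rate to interpret what happens in the INTERCOG arm.

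**Working it through.** The article states no event rate, safety margin or safety power, so there is no figure to reproduce. The check has three parts.

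**1. Contact with staff trained to report events**

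| Period | INTERCOG | Control |
|---|---|---|
| Weeks 1–12 | 12 × 2 = 24 home sessions | 0 described |
| Month 3 to month 9 | none described | none described |

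The second row covers 9 − 3 = 6 of the 9 months.

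Other sections do not supply a both-arm route:
- Baseline and postintervention follow-up lists no item that asks about adverse events, falls, injuries or admissions since the last visit. The Tinetti tool scores fall risk; it does not count falls. The Patient Characterization Form records history and is not described as event capture.
- Intervention fidelity and standardization has co-investigators make unannounced visits and calls, but their stated purpose is adherence.
- The elimination criteria would note death and institutionalization of more than one week in either arm, but only during the intervention phase.

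**2. What the INTERCOG arm alone can show**

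Inputs: 51 patients per arm and 15% attrition (Sample size), so 0.85 × 51 ≈ 43 remain. The true rates are assumptions.

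- Chance of at least one affected patient, 1 − (1 − p)^51: 64% at p = 2%, 93% at 5%, 99.5% at 10%.
- One-sided 95% upper limit if no patient is affected, 1 − 0.05^(1/n): 5.7% for n = 51 and 6.7% for n = 43.

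The arm therefore gives usable descriptive information.

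**3. What unequal capture does to a comparison of arms**

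Let both arms have the same true proportion p of patients with an event. Let INTERCOG capture be complete and control capture be a fraction c. The expected apparent excess is p − cp = p(1 − c), although the true difference is zero. Both p and c are assumptions.

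The chance that such a table would reach two-sided p < 0.05 with 51 per arm was obtained in two ways. The first is the normal approximation, Φ{[p₁ − p₂ − 1.96√(2p̄(1 − p̄)/n)] / √[(p₁(1 − p₁) + p₂(1 − p₂))/n]}, with p₁ = p, p₂ = cp and p̄ their mean. The second sums binomial probabilities over all tables with a Fisher exact p value of at most 0.05. With no control events, Fisher's test needs 6 INTERCOG patients with an event (6 v 0 gives p = 0.027; 5 v 0 gives p = 0.056).

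| True rate, both arms | c | Apparent excess (points) | Normal approx. | Fisher exact |
|---|---|---|---|---|
| 5% | 0 | 5 | 36% | 4% |
| 5% | 0.5 | 2.5 | 10% | 1% |
| 10% | 0 | 10 | 64% | 40% |
| 10% | 0.5 | 5 | 16% | 7% |
| 20% | 0 | 20 | 93% | 96% |
| 20% | 0.5 | 10 | 29% | 20% |
| 30% | 0 | 30 | 99% | 99.9% |
| 30% | 0.5 | 15 | 44% | 36% |

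At low rates the normal approximation is unreliable and the exact column should be preferred. With equal capture (c = 1) the expected excess is 0 and the false-signal probability is at most the nominal 5%.

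**The case against.** The strongest reply is that this argues from silence in a condensed article. The text does not say that delivery staff are the sole source. The sentence sending all events to the principal investigator is not limited to one arm, and it refers to a protection policy that is not shown. Supplementary Table S3, with further assessment details, is not shown either. This part stands: a reader might infer that control events are not ascertained at all, and the document does not establish that. It supports only the statement that no route for them is described. The reply does not remove the point, because the one mechanism the article sets out depends on arm.

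Second, a reader might infer that the pilot cannot judge the safety of the exercise component, or that safety rests on participants' perception alone. Neither is supported. Trained staff attend the home sessions, so exercise-related events in the INTERCOG arm can be counted and bounded, as shown above.

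Third, no between-arm test of adverse events is planned, and safety is neither a listed outcome nor a benchmark. That is correct. The false-signal figures show what would happen if such a table were compiled and tested; they do not describe an error in a planned analysis.

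Fourth, supervised exercise ends at week 12, so months 3 to 9 matter less for harm from that component. This also stands, although background events continue in both arms throughout.

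Finally, having blinded assessors ask about injuries may reveal allocation. Blinding already asks participants not to discuss their activities with evaluators. The risk is real but small, and it shapes the fix.

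**Conclusion.** The concern holds in a limited form. The described adverse-event route depends on arm for the first 12 weeks (24 contacts against none described), and no scheduled query is described for either arm over the remaining 6 of 9 months. Event counts from that route would not be comparable between arms, and background events could not be separated from harm due to the intervention. The distortion runs against INTERCOG: the apparent excess is p(1 − c), for example 10 points at an assumed 10% rate with no control capture, or 5 points with half captured.

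These sizes rest on assumed rates, assumed control capture and complete INTERCOG capture. The conclusion about comparability needs none of those values; it needs only that capture differs by arm. If a document not shown already contains a both-arm query, one clarifying sentence in the article resolves the matter. This is a cheap improvement. It does not put the pilot's feasibility aims in doubt.

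**What to change.** Add one identical, neutrally worded item to the existing 3-, 6- and 9-month assessments in both arms, covering falls, injuries, hospital admissions and other events since the last visit. Base any between-arm safety summary on that item alone. List events reported by delivery staff separately, as surveillance of the INTERCOG arm. State this in Data management and monitoring and add the item to the assessment schedule. If it is not added, limit safety statements to a descriptive INTERCOG-arm rate and say that no comparison with control is intended.

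The cost is a short form and a few minutes at visits that already take place, with no extra staff. To limit unblinding, ask the item after the cognitive tests or use a self-completed form, and do not ask what the participant was doing at the time. The change should be made early, because events missed at visits already completed are hard to recover.
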